## Abstract

**Introduction:** Parkinson's disease (PD) is a chronic, neurodegenerative disease of the central nervous system (CNS). Complications in PD are related to impaired cardiorespiratory capacity, and the presence of motor and nonmotor symptoms, such as reduced cardiorespiratory fitness, decreased respiratory muscle strength and lung volumes and capacities, bradykinesia, muscle rigidity, attenuation of strength and lower limb muscle power, sleep disorders, anxiety, and depressive symptoms. The practice of high-intensity exercise and the examination of the aquatic environment may help to minimize these symptoms and slow disease progression.

**Objective:** To develop a water physical exercise program (WPEP) focusing on high-intensity interval training (HIIT) for individuals with DP.

**Methods:** This is a protocol for a single blinded controlled clinical trial. The sample will consist of individuals with PD between Stages 1 and 4 on the Hoehn and Yahr (HY) Scale, divided into a control group and a WPEP group (which will participate in the WPEP). The outcomes will be divided into three categories: cardiorespiratory, motor, and nonmotor aspects. The WPEP will last 12 weeks, and the intervention will take place two times a week, with a duration of approximately 35 min, with an interval between 48 and 72 h between training sessions for muscle recovery, for a total of 24 sessions. It is expected that this study will establish parameters for prescribing and monitoring a WPEP for individuals with PD Stages 1–4 on the HY scale, enhancing the practice of exercise prescription.

**Trial Registration:** Brazilian Register of Clinical Trials: RBR-3hp5yvh

## 1. Introduction

Parkinson's disease (PD) is the world's fastest growing neurological disease, with biological and socioeconomic consequences [1]. It is also considered a neurodegenerative disease, with chronic and progressive development and multifactorial etiology, involving protein and mitochondrial dysfunctions, degeneration of dopaminergic neurons in the substantia nigra of the mesencephalon, with the influence of genetic, environmental, and age-related factors [2, 3].

Individuals with PD may exhibit motor signs such as bradykinesia, muscle rigidity, resting tremor, and postural instability, in addition to the nonmotor symptoms, ranging from cognition to the functioning of the autonomous nervous system, such as constipation, sexual dysfunction, and sleep disorders, which can directly affect quality of life [4, 5].

Studies have showed that reducing sedentary behavior and increasing the frequency and intensity of physical exercise may help to stabilize and prevent disease progression [6, 7]. In addition, prescription muscle-building and flexibility exercises, as well as proprioceptive and aerobic training are recommended for older adults and individuals with chronic health conditions [8].

Aerobic exercise, especially when prescribed at moderate to high intensity, leads to structural changes in the central and peripheral nervous systems, which lead to brain plasticity and the improvement of body functions and structures in individuals with PD [9, 10]. Thus, the literature has broadened the discussion on high-intensity aerobic exercises for individuals with PD, particularly on high intensity interval training (HIIT), due to its dynamicity, time savings, and prior results equal to or greater than moderate-intensity aerobic training [6, 7, 11].

HIIT is defined by short bouts of high-intensity exercise followed by passive recovery or moderate intensity (active), with running on treadmill or cycling on a ground cycle ergometer being frequently performed activities [7, 12, 13]. Studies have showed the safety of HIIT for individuals with PD, with rare reports of serious adverse events caused to study participants. However, nonsevere adverse effects may still occur, such as falls and pain due to the type, intensity, and speed of the prescribed exercise and the health condition of the person with PD [13–15].

As a result, the execution of aerobic exercises in the aquatic environment emerges as an alternative, as the effect of the heated water's physical properties, such as floatability and viscosity, may improve reaction time and therefore reducing the risk of falls [16–18]. Similarly, the temperature of the water acts on free nerve endings and mechanoreceptors, reducing the conduction of painful stimuli, and increasing blood flow caused by vasodilation. This may provide reduction in muscle tension and joint stiffness, making movement in the water more pleasant and reducing pain perception [16, 18, 19].

Clinical protocol studies are responsible for ensuring standardization of a treatment program, ensuring that the program can be replicated and adapted by other teaching, research, and assistance institutions in a regulated, safe, ethical, and effective manner. To date, we are unaware of any studies that have performed HITT in a heated pool for individuals with PD. Therefore, the objective of this study is to design a program of aquatic physical exercises (WPEP) focusing on HIIT for individuals with PD.

## 2. Materials and Methods

### 2.1. Study Design

This is a protocol for a controlled single blinded clinical trial [20].

The project was approved by the Ethics Committee of the Federal University of Paraná under number 39816320.1.0000.0102. The WPEP study protocol was developed based on the recommendations for clinical trial protocols of the Standard Protocol Items: Recommendations for Interventional Trials (SPIRIT) [21]. This is a high-intensity aquatic physical exercise program to be conducted with individuals with a clinical diagnosis of PD, which will be assessed in two phases, prior to the start of the program and after its completion.

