### 2.4. Assessments

All assessments will be performed at the “on” stage of dopaminergic medication, approximately 1 h after intake. The assessment instruments will take place in three stages: Assessment 1 (initial), followed by 12 weeks of intervention or control period; Assessment 2, after the intervention period or control of the study; Assessment 3, after a 4-week follow-up (no intervention).  Figure 1 shows the sequence of evaluations and interventions.

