#### 2.9.2. Allocation

The allocation will be carried out randomly with support from the Sealed Envelope website (https://www.sealedenvelope.com/simple-randomiser/v1/lists). The subjects will be divided into an intervention group and a control group for a 12-week period. Following this period, participants in the control group will have the opportunity to participate in the WPEP.

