### 2.10. Statistical Analysis

The data will be analyzed for sphericity and homogeneity with Shapiro–Wilk test. The ANOVA mixed model will be used to compare pre- and postintervention and intergroup comparisons. Afterward, a Bonferroni post hoc analysis will be performed on variables with statistically significant differences to identify which assessments differ from each other. The statistical power will be *p* > 0.05, and the effect size will also be shown. SPSS 20.0 statistical software will be used in all the analyses.

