Studies that used the interval training methodology in individuals with PD performed on the ground employed activities that used treadmill and cycle ergometer [7, 11, 12, 15] with diversified parameterization. Malczynska-Sims et al. [15] performed 10 stages of 4 min, with 2 min for cycling in the fast stage and 2 min for the slow stage, and the training range was individualized and progressive according to the weeks and the maximum heart rate (60%–80%). Fernandes et al. [7] employed walking/jogging for 25 min with 1 min in the subjective perception of exertion 15–17 and 2 min between 11 and 13. Harvey et al. [11] conducted a feasibility study for HIIT using circuit dynamics and functional exercises, with four exercises performed at 85% of the maximal heart rate for 45 and 15 s of interval/rest without severe adverse effects. All these previous studies showed that HIIT on the ground is a safe modality for individuals with PD, in terms of adherence, participation, and increase in the physical and functional capacity. These findings may be used as a basis for interval training in an aquatic environment, since the literature on this subject is limited.

Finally, this WPEP was developed to assess this type of clinical intervention in PD population in an aquatic setting. The present clinical trial may have the following limitations: (1) the difficulty in recruiting and adhering to the study for 12 weeks plus the pre- and postintervention evaluation period; (2) the inability of participants to travel to the center where the study will be conducted, particularly Stage 4 participants; (3) difficulty in reaching target intensity due to changes in the autonomic nervous system and heterogeneity of the PD population. Furthermore, the WPEP does not include the use of an individual aquatic heart rate monitor (e.g., an aquatic heart rate monitor) during the intervention period to detect changes in the heart rate during immersion. All these limitations must be considered in future research.

However, details in the description of training and its prescription based on individuality and periodic progression, as well as easiness to apply and cost-effective assessments, may facilitate the WPEP clinical reproducibility.

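### The article gives both two and three assessments and does not say whether Assessment 3 enters the mixed ANOVA, so the group-by-time test can be run in two different ways

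*Protocol article*

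**What the plan says.** Four places in the protocol article bear on the number of assessments.

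- Section 2.1 (Study Design) describes a programme for people with PD, "which will be assessed in two phases, prior to the start of the program and after its completion".
- Section 2.4 (Assessments): "The assessment instruments will take place in three stages: Assessment 1 (initial), followed by 12 weeks of intervention or control period". Assessment 2 follows that period. The list ends with "Assessment 3, after a 4-week follow-up (no intervention").
- Section 2.10 (Statistical Analysis): "The ANOVA mixed model will be used to compare pre- and postintervention and intergroup comparisons". The same section plans a sphericity check ("The data will be analyzed for sphericity and homogeneity with Shapiro–Wilk test") and a Bonferroni step "to identify which assessments differ from each other".
- Section 3 (Discussion) names as a limitation the difficulty of "adhering to the study for 12 weeks plus the pre- and postintervention evaluation period". It does not mention a follow-up visit.

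Section 2.9.2 (Allocation) adds, about the 12 weeks: "Following this period, participants in the control group will have the opportunity to participate in the WPEP". It does not place this before or after Assessment 3.

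**The concern.** The number of assessments fixes the number of levels of the time factor. A group-by-time test with two levels asks whether the groups differ in their change over 12 weeks. With three levels it is an omnibus test, which can be significant because of the 12-week difference, the follow-up difference, or a mixture of the two. It can also miss a 12-week difference that the two-level test would find.

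If the plan does not say which applies, the analyst chooses, possibly after seeing the data, and the choice recurs for every primary outcome in sections 2.5 and 2.6. The Bonferroni comparisons are run only where the first test is significant, so the choice also decides which outcomes reach that step.

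**Working it through.** **Step 1. The text side by side.**

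| Place | Fits two levels | Fits three levels |
|---|---|---|
| 2.1 | two phases, before and after | |
| 2.4 | | three numbered assessments |
| 2.10, model sentence | pre- and postintervention | |
| 2.10, sphericity | | can fail only with three or more levels |
| 2.10, Bonferroni | | for the time factor, has content only with three or more levels |
| 3, limitations | pre and post evaluation only | |

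No visible sentence says which assessments enter the model.

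**Step 2. Degrees of freedom.** From section 2.9.6: N = 30, in g = 2 groups of n = 15. For m time levels, df1 = (g − 1)(m − 1) and df2 = (N − g)(m − 1).

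- m = 2: F(1, 28), 5% critical value 4.20. This equals a t-test comparing change between groups.
- m = 3: F(2, 56), 5% critical value 3.16.

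**Step 3. Power under each version.** The article gives no effect size, SD or correlation, so these are assumptions: unit SD, a 0.8 SD group difference at Assessment 2, equal correlation r between assessments, two-sided 5%, no dropout. Let e be the vector of group differences over time. The noncentrality is λ = 2n × Σ[(e − mean e)/2]² / (1 − r).

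- Two levels, e = (0, 0.8), r = 0.5: the squared deviations sum to 0.32, so λ = 30 × 0.08 / 0.5 = 4.8.
- Three levels, half retained, e = (0, 0.8, 0.4): the sum is again 0.32 and λ = 4.8, now tested on 2 df.
- Three levels, all retained, e = (0, 0.8, 0.8): the sum is 0.4267, so λ = 30 × 0.1067 / 0.5 = 6.4. With none retained, e = (0, 0.8, 0), the sum and λ are the same.

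| Test | r = 0.5 | r = 0.7 |
|---|---|---|
| Two-level F(1,28) | 56% | 78% |
| Three-level F(2,56), half retained | 46% | 69% |
| Three-level F(2,56), all or none retained | 59% | 82% |
| Assessment 2 adjusted for Assessment 1 (ANCOVA) | 67% | 83% |

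The ANOVA rows are analytic, from the noncentral F. The ANCOVA row comes from simulation with 40,000 trials per scenario.

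**Step 4. Both versions on the same data.** The same simulations applied both ANOVA versions to each simulated trial. In the scenarios with an effect, they disagreed on significance in about 12% to 18% of trials. With no effect, each version held about 5%, but at least one was significant in about 7.5% to 8% of trials for a single outcome.

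**The case against.** The strongest reply is that section 2.4 is the dedicated, numbered description and 2.1 only a one-sentence summary. Assessments 2 and 3 both come after the programme ends, so two phases might mean before and after, with two visits in the second. Section 2.10 read as a whole leans towards three levels. On this view the defect is loose wording, not two rival models. Much of this stands: three levels is the more coherent reading, although the sphericity clue is weakened because the test named there is a test of normality. What remains is that the only sentence describing the model's comparisons speaks of pre and post, and nothing says that Assessment 3 belongs in it.

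A reader might go further and infer that the three-level test is contaminated because controls have already been offered the programme by Assessment 3. The documents do not show this. Section 2.4 labels the follow-up as free of intervention, in a sequence covering both groups, and section 2.9.2 gives no order. Figure 1, which may show the sequence, is not available here. The order is an open question.

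A reader might also say that the trial's main between-group test has two definitions. The article names no such test. Group by time is the natural reading of a mixed ANOVA with a group comparison, but it is a reading.

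Finally, a full protocol or SAP may specify the model. That would supply missing detail, but the article's own statements would still disagree and need correcting.

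**Conclusion.** The contradiction is real and lies in current text. Sections 2.1 and 3 describe two assessment points, section 2.4 describes three, and section 2.10 leaves open whether the third enters the ANOVA. The two possible group-by-time tests have different null hypotheses and degrees of freedom. In the scenarios examined, three-level power ranges from about 10 points below to about 4 points above two-level power.

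These sizes are illustrative. They rest on an assumed 0.8 SD effect, equal correlations of 0.5 or 0.7, and full follow-up of 15 per group. They show that the choice can change a conclusion, and in either direction. They do not show how far this trial's results would move. The point should be corrected before analysis. It does not invalidate the design.

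**What to change.** 1. Make sections 2.1, 2.4, 2.10 and the limitations paragraph of section 3 agree on the number of assessments.
2. In 2.10, state that the between-group conclusion for each primary outcome rests on the group difference at Assessment 2, adjusted for the Assessment 1 value. This isolates the 12-week randomised comparison and uses a baseline that is already collected. Under the assumptions above, its power is higher than that of either ANOVA version, though at r = 0.7 only marginally higher than the three-level test with all or none of the effect retained. If the mixed ANOVA is kept instead, the minimum is to name the time points in it and the contrast that carries the conclusion.
3. Report Assessment 3 separately, as secondary.
4. Reconcile 2.4 and 2.9.2 on whether controls can start the programme before or after Assessment 3, so that readers know what the follow-up comparison means.

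The cost is wording in these sections and one model specification, with no new data. The small downside is that Assessment 3 no longer contributes to the primary test.

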### 2.2. Participants

Individuals with a clinical diagnosis of PD and classified in Stages 1–4 of the Modified Hoehn and Yahr (HY) Scale, residing in the city of Curitiba (PR), of both sexes, and vaccinated against COVID-19 will be invited to participate in the study, with consent to participate in the study voluntarily and sign the free and informed consent term (FICF).

The exclusion criteria will include cognitive, visual, and auditory impairments, as well as the use of wheelchairs (whether due to or not due to PD), cardiovascular surgery, or decompensated cardiac diseases that place the participant at risk, or any absolute contraindication to attend a heated swimming pool, and changes in dosages or parameters of the medication associated with PD during the course of the study [22, 23].

### 2.3. Recruitment

The study will be announced via digital media and at the Parkinson's Association Paraná. A telephone call will be made to potential participants to formalize the invitation to participate and to discuss the eligibility and exclusion criteria with each interested individual. They will also be informed about voluntary participation in the study and the need to sign the FICF.

### 2.4. Assessments

All assessments will be performed at the “on” stage of dopaminergic medication, approximately 1 h after intake. The assessment instruments will take place in three stages: Assessment 1 (initial), followed by 12 weeks of intervention or control period; Assessment 2, after the intervention period or control of the study; Assessment 3, after a 4-week follow-up (no intervention).  Figure 1 shows the sequence of evaluations and interventions.

### 2.5. Primary Outcomes—Cardiorespiratory Aspects

1. Cardiorespiratory performance—6-minute walking test (6-MWT)  The 6-MWT is a submaximal test used to indirectly measure cardiorespiratory fitness, functional capacity to exercise, walking distance, and walking observation, and it is a predictor of morbidity and mortality [24]. The incentive phrases and the full test will be conducted according to the guidelines for the 6-MWT of the American Thoracic Society [24].2. Heart rate variability (HRV)—Heart rate sensor  The HRV will be collected using a Polar H10 heart rate sensor, which will be placed slightly below the xiphoid process. The participant will remain lying down, quietly, in dorsal decubitus position for 10 min, with spontaneous breathing. The data will be exported in txt format to the *Kubios HRV Standard* 3.4.2 software, where ectopic beats, signs of artifacts, and sinus beats with less than 95% will be excluded from the study [25].  For the analysis in the time domain, the SDNN values, resulting from the standard deviation of all normal R-R intervals, representing sympathetic and vagal modulation, and the RMSSD, corresponding to vagal modulation, will be obtained by the square root of the mean square of the differences between adjacent normal R-R ranges minus one. The frequency domain is composed of the high frequency (HF), which indicates the activity of the vagus nerve on the heart, the low frequency (LF), which represents both the vagal and sympathetic components on the heart, with predominance of the sympathethic, and the LF/HF ratio that characterizes the sympathovagal balance [26, 27].3. Pulmonary volumes and capacities—spirometry  The examination of forced vital capacity (FVC), forced expiratory volume in 1 s (FEV-1), Tiffeneau–Pinelli Index (VEF1/FVC ratio) and maximal voluntary ventilation (MVV) will be performed using a portable spirometer.4. Maximal inspiratory pressure and maximal expiratory pressure—manuvacuometer  The maximal inspiratory pressure (MIP) and maximal expiratory pressure (MEP) are correlates of respiratory muscle strength (inspiration: diaphragm and intercostal muscles; expiration: abdominal muscles) and are measured in centimeters of water (cmH_2_0) using manovacuometry [28].

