### 2.6. Primary Outcomes—Motor Aspects

1. Activities of daily living (Section 2) and motor symptoms (Section 3)—Unified Parkinson's Disease Rating Scale (UPDRS)  The UPDRS scale has 4 sections, and in this study only Section 2 and Section 3 will be used, in order to measure the progression of the disease through the participants self-report. Each item is scored from 0 to 4 points, with the higher and lower values corresponding to greater and less disease severity, respectively [29].

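### Five primary items, which expand to 14 named variables, have no lead outcome and no error control across them

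*Protocol article*

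**What the plan says.** Section 2.5 of the Protocol article, headed "Primary Outcomes—Cardiorespiratory Aspects", has four numbered items: the 6-minute walking test (6-MWT), heart rate variability (HRV), spirometry, and maximal inspiratory and expiratory pressure. Section 2.6, headed "Primary Outcomes—Motor Aspects", adds the UPDRS, restricted to Sections 2 and 3. Several items name more than one variable. HRV, for example, runs from SDNN and RMSSD to "the LF/HF ratio that characterizes the sympathovagal balance".

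Sections 2.7 to 2.9 carry separate secondary headings, so the primary label is a deliberate tier. Within that tier nothing is ranked.

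Section 2.10 plans a mixed ANOVA for the pre/post and between-group comparisons. It then says that "a Bonferroni post hoc analysis will be performed on variables with statistically significant differences to identify which assessments differ from each other". No other adjustment is described. Section 2.9.6 sets the sample at 30 (15 per group) without naming an outcome.

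**The concern.** When several variables share primary status and each is tested at the same threshold, the chance that at least one is significant by luck grows with their number. The Bonferroni step may look like protection, but it acts inside a variable that has already passed its own test, and its stated purpose is to find which assessments differ. It does nothing to the number of variables that pass by chance.

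What is at stake is the meaning of a positive result. The Discussion says that favourable findings on the assessed aspects could lead to further studies that guide practice, but it does not define favourable. The plan would leave a reader unable to tell a trial that met its objective from one in which a single HRV or spirometry index crossed the threshold.

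**Working it through.** **Inputs from the Protocol article**

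| Item | Section | Variables | Running total |
|---|---|---|---|
| 6-MWT | 2.5 | 1 | 1 |
| HRV: SDNN, RMSSD, HF, LF, LF/HF | 2.5 | 5 | 6 |
| Spirometry: FVC, FEV1, FEV1/FVC, MVV | 2.5 | 4 | 10 |
| MIP, MEP | 2.5 | 2 | 12 |
| UPDRS Section 2, Section 3 | 2.6 | 2 | 14 |

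There are five numbered items and 14 variables when every named index is counted.

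**Assumptions**

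- The threshold is 0.05, two-sided. Section 2.10 miswrites it as a statement about power with the inequality reversed, but no other reading is plausible.
- There is one deciding test per variable, the group-by-time interaction.
- There is no true effect on any variable.
- Correlations among the variables are not given, so a range is used.

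The document states no familywise error rate, so there is no figure of its own to reproduce.

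**Independent tests.** The chance of at least one false positive in k tests is 1 − (1 − 0.05)^k.

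- k = 14: 1 − 0.95^14 = 0.512
- k = 5: 1 − 0.95^5 = 0.226

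**Correlated tests.** Simulation of 14 two-sided z tests with a common correlation (300,000 draws):

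| Common correlation | At least one false positive |
|---|---|
| 0.3 | 43.7% |
| 0.5 | 34.7% |
| 0.7 | 24.9% |
| 0.8 | 19.7% |
| 0.9 | 14.1% |

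Two variations give similar answers. Two-sample t-tests with 15 per arm (20,000 draws) give 51.2%, 35.7% and 26.2% at correlations of 0, 0.5 and 0.7. Letting correlation be higher within an instrument (0.5 to 0.9) than between instruments (0 to 0.5) gives 26.6% to 45.9%.

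**With control.** A single primary variable has an error rate of 5%. Bonferroni across 14 uses 0.05/14 = 0.0036 each. The familywise rate is then 1 − (1 − 0.05/14)^14 = 4.9% under independence and at most 5% under any correlation. Holm also holds it at 5% or less and is never less powerful than Bonferroni.

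**Price of keeping all 14.** For a simple two-sample t-test with 15 per arm that ignores baseline, the difference detectable with 80% power is about 1.06 SD at 0.05 and about 1.48 SD at 0.05/14. Using baseline lowers both. For a change score at an assumed pre/post correlation of 0.8, the factor is √(2 × (1 − 0.8)) = 0.632, which gives about 0.67 and 0.94 SD.

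**The case against.** The strongest reply is that the article declares five items, not 14, and that a condensed article may leave the index carrying each instrument to the full protocol or SAP. Part of this stands. Fourteen is the full expansion, so it should not be read as a minimum. But five unranked primaries still give 23% under independence. The defect is also not missing detail: the article itself assigns the primary tier and itself states a multiplicity step that does not cover it.

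A second reply is that no rule says one significant primary is enough. That is true, and a reader who infers an any-one-wins rule goes beyond the text. Equally, no rule requires all primaries to succeed or picks one out, so the plan does not exclude that use.

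Two stronger readings are tempting and do not hold:

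- **A minimum risk of 25%.** That figure belongs to an assumed common correlation of 0.7. At 0.9 the risk is about 14%.
- **Forty-two tests**, from three F-tests on each of 14 variables. The time main effect pools both arms and does not test the intervention, and section 2.10 does not say that any of the three F-tests decides success. One interaction test per variable is the fair count.

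The stated objective, to develop the programme and its prescription parameters, softens the consequence somewhat. It does not remove it, because the trial still carries a declared primary tier and significance testing.

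**Conclusion.** The concern holds in this form: five primary items, or 14 variables in full, share primary status with no lead outcome, and the planned Bonferroni step gives no protection across them. With one test per variable at 0.05 and no true effect, the chance of at least one false positive primary is 51% for 14 independent tests, about 35% at a common correlation of 0.5, about 25% at 0.7 and about 14% at 0.9. With one index per item it is 23% under independence.

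The correlations are assumptions, so no single figure can be given for this trial. The direction does not depend on them: every case examined is nearly three times the nominal 5% or more.

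**What to change.** Before the data are analysed, name one primary variable, one time point and one contrast. An example is 6-MWT distance, between-group comparison of the change from Assessment 1 to Assessment 2, at two-sided 0.05. It is offered because it is listed first, under "Cardiorespiratory performance—6-minute walking test (6-MWT"). It should not be justified as a direct measure of fitness, since section 2.5 describes it as an indirect one. The sponsor may justify another variable.

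Move the remaining variables to secondary, either with Holm across them or as exploratory estimates with 95% confidence intervals.

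The alternative is to keep several primaries, list exactly which indices they are, and apply Holm across that set. The within-variable Bonferroni step can stay for its own purpose.

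The cost is edits to sections 2.5, 2.6 and 2.10 and a registry update. No measurement changes. Fewer outcomes can carry a confirmatory claim. If all 14 are kept with correction, each has lower power, as the rise from about 1.06 to about 1.48 SD shows. The Discussion describes the assessments in the past tense, so if data collection has begun, the change should be dated and its reasons recorded.
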